*Adaptation of g-IPT*: IPT had been previously adapted to the Kenyan and Lebanese contexts for cultural and situational relevance in earlier studies [42–44]. However, further refinements have been made for this specific study population and regional contexts. These adaptations in content and delivery of g-IPT contemplate each location’s cultural norms for young mothers related to intimacy, authority, daily routines, interactions, child-rearing practices, and communication standards (like expressions of closeness, including mother–child attachment, aggression, assertiveness, etc.). Also considered are the current societal, familial, and individual stressors arising from social instability, increased poverty, and scarce resources, which are prevalent in both regions, albeit in varied forms. Notably, issues like domestic violence and grave livelihood challenges are anticipated to be pertinent for both nations. These adaptations were meticulously documented during the pre-trial and feasibility stages, employing the Framework for Modification and Adaptations-Enhanced [45]. Feedback from participants in the feasibility trial was integrated iteratively, refining the g-IPT model, which culminated in the final clinical protocol to be assessed in the RCT.

*g-IPT training*: For the sake of sustainability and scalability, the qualifications of g-IPT providers will differ between the two study sites. In Lebanon, in line with recent national regulations for accredited psychotherapy provision, trial providers will be licensed psychologists associated with primary care locations, with one facilitator per group. In contrast, Kenya, which has adopted a task-shifting approach to bolster capacity in primary care [46], will utilise community health workers, assigning two facilitators per group. Supervisors across both sites will be professionals previously trained in IPT, such as psychologists, psychiatrists, and social workers. The training and implementation of the intervention will be overseen by two US-based g-IPT master trainers.

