We will adopt the apprenticeship model of psychotherapy training, which entails a three-tiered system for sustainable capacity building: master trainers, local supervisors, and g-IPT providers [47, 48]. The master trainers, aided by local supervisors, will conduct a 4-day didactic g-IPT workshop for facilitators. This will be followed by a standardised g-IPT knowledge test with a set “pass” threshold. Facilitators who pass this test will subsequently receive supervision in weekly meetings (either onsite or online) for two groups per facilitator. These sessions will be led by the local supervisors, with occasional assistance from the master trainers. Facilitators’ competence will be gauged using a g-IPT fidelity checklist during these supervision sessions. Only facilitators who achieve a mean score per group that meets or exceeds 75% of the “adequately competent” benchmark at designated intervals (one during the pre-group phase, one at the outset, two mid-way, and one at the end) will be certified to conduct the study. Following the completion of their inaugural training case, trainees will attend a 2-day advanced workshop. Orchestrated by master trainers and local supervisors, this workshop will fortify both knowledge and expertise.

Priority will be given to supporting both facilitators and supervisors, especially considering they are contending with persistent socioeconomic challenges in both regions. A communal spirit of mutual support and collaboration will be cultivated via group supervision and inter-site conferences. These gatherings will facilitate the exchange of experiences, ideas, and assistance in applying the IPT model.

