### Sample size {14}

Power calculations indicate that a sample of 412 participants (*N* = 224 in the g-IPT arm and* N* = 188 in the control arm) offers 90% power to detect a standardised mean difference of 0.40 on the primary outcome, allowing for up to 25% attrition. These calculations are based on a predetermined effect size of 0.4, as informed by the Cuijpers et al. meta-analysis [29], on the primary outcome [62]. They also consider a two-tailed alpha level of 0.05 and account for clustering with an intra-class correlation (ICC) of 0.04 [63] in the treatment arm, further adjusted for an expected attrition rate of 25% [64]. The sample size estimates were derived using the “clsampsi” routine in STATA, with the assumption of a g-IPT group size of 8.

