## Statistical methods

### Statistical methods for primary and secondary outcomes {20a}

All quantitative analyses will be conducted on an intention-to-treat (ITT) basis at the NWORTH Clinical Trials Unit. A comprehensive statistical analysis plan will be drafted and approved by the trial team before data collection concludes and will be open for review by independent committees.

Baseline characteristics will be summarised both overall and by treatment group (intervention and control), as well as by site subgroup. Descriptive statistics for all outcome variables will be generated at every time point.

Categorical variables will be showcased with counts and percentages. Continuous variables will be represented using means, standard deviations, and ranges. For non-normally distributed continuous variables, medians and interquartile ranges will be used.

The CONSORT details will be furnished with data on participant numbers.

The primary analysis will evaluate MDAT scores at 52 weeks post-initial clinical contact. A general linear mixed model will be employed, which accounts for clustering in the intervention arm. This model will adjust for allocation group and study centre. Additional covariates or factors to be integrated into the model will be pre-determined in the SAP. All statistical tests will be two-sided and paired with 95% confidence intervals.

Analyses will be executed in STATA or R, adhering to the ITT principle. The significance level (alpha) will be set at 5% (two-tailed). Linear mixed modelling, taking into account clustering by g-IPT group in the treatment arm, will be used, controlling for stratification factors (site and age group). It will also account for pre-defined covariates and model the longitudinal effects of time, as well as any pertinent time-treatment interactions.

Secondary outcomes will be evaluated using a comparable model suitable for the outcome type and will factor in baseline measures where relevant, in addition to stratification and pre-defined covariates.

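### The primary MDAT model names g-IPT group as its only clustering level; if facilitators lead several trial groups, type I error may exceed 5%

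*Protocol article*

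**What the plan says.** The Protocol article, Statistical methods {20a}, fixes the clustering structure of the primary model: "Linear mixed modelling, taking into account clustering by g-IPT group in the treatment arm, will be used". The same section sets alpha at 5% two-sided and leaves further covariates or factors to the SAP.

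Sample size {14} uses the same single level. It has "a sample of 412 participants", with "224 in the g-IPT arm" and 188 controls, an ICC of 0.04 in the treatment arm, "with the assumption of a g-IPT group size of 8", and the claim that this "offers 90% power to detect a standardised mean difference of 0.40 on the primary outcome, allowing for up to 25% attrition".

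Intervention description {11a}, under g-IPT training, describes the staffing. Lebanon uses licensed psychologists, "with one facilitator per group"; Kenya uses community health workers, two to a group. Trainees who pass the knowledge test are then supervised "for two groups per facilitator", and must reach a fidelity benchmark before they are certified for the study. No section gives the number of facilitators or the number of trial groups each one leads.

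**The concern.** Two groups led by the same person share that person's skill and style. A model with a group effect only treats them as independent. If facilitators differ in the effect they have on the outcome, the variance of the g-IPT arm mean is understated, the confidence interval for the primary MDAT difference is too narrow, and the test rejects more often than the 5% the protocol fixes.

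Repeat use is an inference, but a strong one. With 224 women in groups of 8 there are 224/8 = 28 groups. Recruitment {15} plans equal monthly numbers per site, so assume 14 groups per country. Using each facilitator only once would then need 14 in Lebanon and 2 × 14 = 28 in Kenya, 42 in all, each trained, supervised on two groups and certified. Recruitment ran from 2 January to 23 October 2023 (Trial status) and a course is nine sessions held weekly, so one facilitator could lead several courses in turn.

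**Working it through.** **Inputs from the protocol.** Alpha 0.05 two-sided, standardised difference 0.40, ICC 0.04 in the g-IPT arm, group size 8, arms of 224 and 188, attrition 25%. Analysed: 224 × 0.75 = 168 and 188 × 0.75 = 141.

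**The plan's own figure.** Design effect in the g-IPT arm = 1 + (8 − 1) × 0.04 = 1.28. SE = √(1.28/168 + 1/141) = 0.1213. Power = Φ(0.40/0.1213 − 1.96) = 91.0% (90.6-90.8% with t degrees of freedom of 160 to 307). The stated 90% reproduces, with about one point to spare.

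**Assumptions for a facilitator level.** All 28 groups contribute, thinned by attrition to 168/28 = 6 analysed women each. The total ICC stays at ρ = 0.04 and splits into ρ_g (group) and ρ_f (facilitator). F is the number of facilitators, or of fixed pairs in Kenya. Neither F nor ρ_f is in the protocol.

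- Variance the group-only model reports: V_model = (1 − ρ)/168 + ρ/28 + 1/141 = 0.005714 + 0.001429 + 0.007092 = 0.014235
- True variance: V_true = (1 − ρ)/168 + ρ_g/28 + ρ_f/F + 1/141
- True type I error of the group-only test: 2 × [1 − Φ(1.96 × √(V_model/V_true))]
- Power of a correctly specified analysis: Φ(0.40/√V_true − 1.96)

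With ρ_f = 0, power is 91.8% and type I error 5.0%.

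Example, F = 14 (two groups each), all of the ICC between facilitators: V_true = 0.005714 + 0.04/14 + 0.007092 = 0.015664. The SE ratio is √(0.015664/0.014235) = 1.049, type I error is 6.2% and power is 89.2%.

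| F | Share of ICC between facilitators | Type I error, group-only model | Power, correct model |
|---|---|---|---|
| 14 | one eighth | 5.1% | 91.5% |
| 14 | one quarter | 5.3% | 91.2% |
| 14 | half | 5.6% | 90.5% |
| 14 | all | 6.2% | 89.2% |
| 10 | half | 6.1% | 89.5% |
| 10 | all | 7.1% | 87.0% |
| 6 | half | 7.2% | 86.9% |
| 6 | all | 9.4% | 81.8% |

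The last two columns describe different analyses. If the group-only test is used despite facilitator variance, its rejection rate at a difference of 0.40 is Φ((0.40 − 1.96√V_model)/√V_true). With all of the ICC between facilitators this is 90.8%, 90.0% and 88.3% for F = 14, 10 and 6; part of that rate is bought by the inflated alpha.

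**Sensitivity to group size.** If the 168 analysed women instead formed 21 full groups of 8, the design effect would be 1.28 + (g − 1) × 8 × ρ_f for g groups per facilitator. For ρ_f = 0.01, 0.02 and 0.04, power is 90.1%, 89.2% and 87.4% at g = 2, and 88.3%, 85.5% and 79.9% at g = 4. True alpha is about 5.4-6.5% at g = 2 and 6.1-9.6% at g = 4.

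**The case against.** The strongest objection is that the premise is not in the document. A reader might take the two groups per facilitator as the trial caseload. The text does not support that: it describes supervised training before certification. If each facilitator led one trial group, or if facilitators did not differ on MDAT, the error would be zero. The outcome is the child's development at 52 weeks, well after a course of about nine weekly sessions given to the mother, so the facilitator share may be small. The source of the 0.04 cannot be examined here, so its split is unknown. All of this stands, and it makes the point conditional.

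A reader might also infer that the 90% power is overstated. It reproduces, and with 14 facilitators it stays within about one point of 90% or above it. The extreme values need six facilitators or pairs for two countries and most of the ICC at that level. Study setting {9} lists eleven recruitment venues and Lebanese providers are tied to primary care locations, so six is a limit of the range, not an expectation.

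Third, the SAP may settle this. It may, but what the protocol defers is covariates and factors; the clustering level it states outright, and a SAP that follows it would fit group only.

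Last, the extra term may be hard to estimate. With 14 facilitators, two groups each and six women per group, an ANOVA estimate of the facilitator variance would be negative about 36% of the time at a facilitator ICC of 0.02 and 24% at 0.04. That is a real limitation. Even so, simulation with a facilitator-level variance brought type I error back to about 4.4-5.9%, although the component was often truncated to zero.

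**Conclusion.** The concern holds in conditional form. The protocol fixes g-IPT group as the only clustering level, and repeat use of facilitators is likely but unstated. Given repeat use and any positive facilitator variance on MDAT, the primary test exceeds its nominal 5%: modestly (5.1-6.2%) with 14 facilitators or pairs, and by more (about 6-9%) with 6 to 10 when half or all of the ICC lies between them. Spare power does not correct this.

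The documents do not show that the standard errors are certainly too small or that the power claim is wrong. Power falls clearly below 90% only with fewer facilitators and a large facilitator share of the ICC. All sizes rest on the assumed F and ρ_f, a total ICC of 0.04, 28 groups and normal approximations.

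**What to change.** Before the SAP is approved, amend the model in Statistical methods {20a} so that the g-IPT arm carries a facilitator random effect above g-IPT group. In Kenya use the facilitator pair, or a multiple-membership term if pairs change between groups. Use small-sample degrees of freedom that reflect the number of facilitators. At minimum, pre-specify this as a sensitivity analysis of the primary MDAT comparison. State in advance what happens if the facilitator variance is estimated at zero. Report both ICCs and the number of trial groups per facilitator, and show power over a range of facilitator ICCs beside the 90%.

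The cost is analysis wording and one variance term. Facilitator identity should already be on record, because fidelity is scored by facilitator. The price is a slightly wider confidence interval and a component that may be estimated at zero.

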### Interim analyses {21b}

There is no planned interim analysis for the study.

### Methods for additional analyses (e.g. subgroup analyses) {20b}

The Statistical Analysis Plan will detail all intended supplementary analyses.

*Health economics*: An economic evaluation of group interpersonal psychotherapy (g-IPT) versus high-quality standard care (HQ-SC) will be undertaken from both provider and participant perspectives. Participant costs will encompass travel, care-seeking, and opportunity costs. Provider costs will be categorised into set-up and implementation and will be approximated using a combination of bottom-up and top-down methodologies. Both financial and economic costs will be determined by considering indirect costs such as volunteer time and donated goods. The results will display the average cost per participant for both g-IPT and HQ-SC from the viewpoints of the provider, participant, and society (combining both provider and participant). The financial expenditure of implementation will estimate the total amount necessary to provide HQ-SC and g-IPT on a larger scale. All outcomes will be delineated separately for Kenya and Lebanon in both local currencies and international dollars.

These costs will be amalgamated with trial outcomes to compute the cost-effectiveness of g-IPT in comparison to HQ-SC. The primary analysis will have a time horizon of 52 weeks, consistent with the trial’s follow-up duration. Net differences in expenses between g-IPT and HQ-SC will be juxtaposed with net differences in outcomes to compute the incremental cost-effectiveness ratios (ICERs). ICER computations will be rooted in primary (PHQ-9) and secondary (quality-adjusted life years) trial results. Sensitivity analyses will probe the influence of varying factors such as analysis duration, pivotal cost components, and the confidence intervals of trial outcomes. The trial’s equity impact will be assessed by analysing income quantiles and measurements of multidimensional poverty. A detailed description of the planned economic evaluation will be presented in a separate health economics protocol.

### Methods in analysis to handle protocol non-adherence and any statistical methods to handle missing data {20c}

For the management of missing data, we will employ a maximum-likelihood multiple imputation method, with a sensitivity analysis juxtaposed against the complete case dataset. The primary analyses will be conducted on an ITT basis. In addition, secondary analyses, encompassing per-protocol and CACE analyses, will be performed to evaluate the potential modification of treatment effect estimates due to diminished clinical engagement.

### Plans to give access to the full protocol, participant-level data, and statistical code {31c}

The study protocol will be publicly available on the sponsor’s website and the dataset will be available upon request to the study’s chief investigator. The statistical analysis plan will be published on Open Science and the code may be available upon request. Legal constraints in both participating countries limit the full implementation of Open Science protocols.

## Oversight and monitoring

### Composition of the coordinating centre and trial steering committee {5d}

The oversight of this trial will be facilitated by four committees: the Data Monitoring and Ethics Committee (DMEC), the Trial Steering Group (TSC), and two local Community Advisory Boards (CABs) situated in Kenya and Lebanon.

*Trial Steering Committee*: The TSC is tasked with the supervision of the trial. It will review the DMEC’s recommendations and, based on this information, suggest any pertinent amendments or actions for the trial. The TSC represents the interests of the funder and Sponsor.

*Community Advisory Boards*: The CABs are established to provide guidance to the study team, thereby enriching the research’s quality, feasibility, and visibility in the community through meaningful local engagement. The CABs are designed to elevate the research’s relevance by collaborating with community partners of varying expertise. Key responsibilities of the CABs include advising on the sustainability and long-term impact of the study, discussing adherence issues, supporting outcome monitoring, and advising on integrating the research findings into the broader healthcare system. Furthermore, they will review training materials to ascertain the sustainability of g-IPT and offer guidance on adapting it to local settings.

### Composition of the data monitoring committee, its role, and reporting structure {21a}

The DMEC comprises independent experts in the respective field. The Committee convenes roughly every 6 months (or as deemed necessary) to scrutinise recruitment, track follow-up rates, and examine serious adverse events. The DMEC serves in an advisory capacity to the TSC and holds the authority to suggest premature closure of the trial. The DMEC operates independently from the sponsor.

### Adverse event reporting and harms {22}

Adverse events (AEs) and serious adverse events (SAEs) will be documented and relayed in alignment with the study’s AE/SAE protocol. The local trial coordinator at each site will report all adverse events to the designated senior clinician for classification. Every AE will be evaluated in terms of its severity, causality, seriousness, and expectedness. All AEs will be relayed to the site’s Principal Investigator (PI), and SAEs will be communicated to the site PI, the programme Chief Investigator (CI), and the independent chair of the DMEC.

This systematic approach ensures consistent responses to AEs and SAEs in accordance with the study’s guidelines. Additionally, the National Mental Health Programme High-Risk Protocol in Lebanon and the Adverse Events Standard Operating Procedures in Kenya will be adhered to.

### Frequency and plans for auditing trial conduct {23}

The sponsor will establish the degree and nature of the required monitoring for the trial. Risk will be continually assessed, and modifications made in response. The extent of monitoring will correlate with the risks associated with the trial. An oversight and monitoring plan tailored to this study will be implemented.

### Plans for communicating important protocol amendments to relevant parties (e.g. trial participants, ethical committees) {25}

Prior to any participant recruitment, the Chief Investigator and the UK study team will ensure that the relevant research ethics committees have approved the trial protocol, participant information sheet, consent form, and other associated documents. Any modifications to the protocol and supporting documents, including approved amendments, will be documented and submitted for the necessary ethical and regulatory approvals. These amendments will not be implemented until the requisite approvals are secured.

Recruitment at local sites will only commence once all local permissions are in order and the UK study team has given the green light via email. It is incumbent upon the CI/PI or their designee at each site to ensure all future amendments obtain the essential approvals, encompassing both UK and local ethical permissions.

In the UK, the REC will receive an annual progress report (APR) within 30 days of the anniversary of its favourable opinion, and this will continue annually until the trial concludes. Additionally, the study representative at UCL in the UK will receive a progress report every 6 months. Within 90 days post-trial completion, the Chief Investigator will notify the main REC that the trial has concluded. If the trial ends prematurely, these notifications will be given within 15 days post-trial conclusion.

A summary report of the trial will be prepared by the CI for the Sponsor, which will then be relayed to the REC within a year after the trial’s conclusion.

In Lebanon, any intended deviation from the protocol must be disclosed beforehand to the USJ (Universite Saint Joseph) IRB. For instance, if there is a desire to alter the recruitment numbers or modify the project’s timeline, a justifying letter must be sent and approval must be acquired from the board.

In Kenya, an annual ethical renewal is mandated during the study duration. This renewal will be facilitated through an annual progress report, submitted to the local ERC 1 month before the yearly approval expires. The study coordinator will draft the APR for this purpose. Upon the study’s culmination, the local ERC will be apprised of its completion by the study coordinator. The annual renewal of NACOSTI and County research permits hinges on the progress report’s submission and the clearance of AE/SAE reporting by the IRB in Kenya.

### Dissemination plans {31a}

The primary medium for disseminating the study’s results will be through publications in reputable peer-reviewed journals. Additionally, these results will be integrated into presentations at conferences, seminars, and workshops. Collaborative partners will also discuss and reference the study in their respective articles and communications. The Community Advisory Boards will advise on key stakeholders in Lebanon and Kenya and strategies to reach them. To reach a wider audience, the findings will also be communicated through press releases, webinars, and informative sessions for healthcare professionals and relevant stakeholders. In Kenya, local engagement will take place at both the County and National levels and policy briefs will be produced. In Lebanon, findings will be disseminated through the design of national mental health campaigns around maternal mental health—specifically post-natal depression. This campaign will include inter-ministerial collaboration (Ministry of Communication, MoPH & others). Evidence-based and culturally adapted key messages will be tailored towards the general public throughout all local media channels and PHC networks in Lebanon. Evidence-based awareness sessions and supporting materials for the general public will be delivered as part of the PHCs’ service to their local communities.

